### Surfactant treatment

Infants in the IN-REC-SUR-E arm will undergo the following approach: as soon as possible after the recruitment maneuver (at CDP_OPT_) a dose of poractant alfa (Curosurf (Chiesi Farmaceutici, Parma, Italy)) of 200 mg/kg will be administered via a closed administration system in one to two aliquots (1–2 min). The tube position will be confirmed by auscultation. A temporary reduction of frequency may be necessary to increase the V_T_ up to 2.5 ml/kg for improving the surfactant spreading.

Infants in the IN-SUR-E arm will undergo the following approach: after intubation, a dose of poractant alfa (Curosurf (Chiesi Farmaceutici, Parma, Italy)) of 200 mg/kg will be administered via a closed administration system in one to two aliquots (1–2 min). The tube position will be confirmed by auscultation. During surfactant administration, infants will be manually ventilated to facilitate surfactant distribution. If necessary, mechanical ventilation with a peak inspiratory pressure (PIP) of 20–22 cmH_2_O, a PEEP of 5–6 cmH_2_O and a respiratory rate of 30–40 breaths/min will be subsequently started to achieve a V_T_ of 4–6 ml/kg and/or to maintain the transcutaneous partial carbon dioxide pressure (TcPCO_2_) between 40 and 60 mmHg (5.3 and 8.0 kPa).

After surfactant administration, the babies of both groups will be extubated within 30 min (if satisfactory respiratory drive is present) and will receive nCPAP (6–8 cmH_2_O) [20]. In case of insufficient respiratory drive, CDP and/or ΔP (in the babies of IN-REC-SUR-E arm) or PIP (in the IN-SUR-E arm) will be reduced until spontaneous respiratory activity is restored, to maintain the transcutaneous partial carbon dioxide pressure (TcPCO_2_) between 40 and 60 mmHg (5.3 and 8.0 kPa). Maintaining a FiO_2_ < 0.30 to obtain SpO_2_ values in the desired range (87–94 %) will drive the eventual reduction in the level of CPAP in the following days. The decision as to whether to begin bi-level nCPAP (BiPAP) or nasal intermittent MV (N-IMV) to prevent the need for re-intubation in infants of both groups will be up to the neonatologist on duty, and will be considered in the final analysis.

Infants of both groups can receive a subsequent dose of surfactant (100 mg/kg of poractant alfa) using the same method (IN-SUR-E or IN-REC-SUR-E) if they meet the CPAP failure criteria again during the following 12 to 24 h.

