### Blinding

The study will not be blinded, and the staff performing the study also will take subsequent care of the infants.

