### CPAP failure criteria

In the NICU, nCPAP will be given through nasal prongs/mask using the standard method of the single centre (ventilator, flow-dependent system) with an initial pressure of 6 to 7 cmH_2_O, in all infants. CPAP failure is defined if they met any of the following criteria: FiO_2_ ≥ 0.30 on nCPAP [17] to maintain a SpO_2_ of 87–94 % [18] for at least 30 min unless rapid clinical deterioration has occurred; respiratory acidosis defined as pCO_2_ > 65 mmHg (8.5 kPa) and pH <7.20 on an arterial or capillary blood gas sample; apnea defined as more than four episodes of apnea per hour or more than two episodes of apnea per hour when ventilation with bag and mask will be required.

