### Primary outcome measure

The primary outcome is the need for mechanical ventilation within the first 3 days of life and, therefore, we consider IN-REC-SUR-E or IN-SUR-E a success if mechanical ventilation is not required and a failure if the infant needs mechanical ventilation in the first 72 h. Infants in both groups will be considered to have reached the primary outcome also when they are not extubated within 30 min after surfactant administration or when they meet the nCPAP failure criteria after extubation.

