
There are some limitations in our study design: (1) surfactant replacement therapy involves instillation of a liquid-surfactant mixture directly into the lung airway tree. Thus, surfactant distribution and efficacy are not only affected by lung recruitment before its administration but also depend on the methodology used for delivery of the drug and on the post-administration ventilatory management (prevention of collapse due to inadequate weaning). In our study, different methods of surfactant delivery will be used between the two groups. In the group of infants submitted to a lung recruitment maneuver, surfactant will be delivered into the airways without disconnection from the high frequency ventilator. The control group will receive surfactant while manually ventilated. On the other hand we cannot recruit and stabilize the lung if we start positive pressure ventilation in the IN-REC-SUR-E group, just to recruit at the time of administration of surfactant and delivery of positive pressure ventilation before/after its use. Recruitment is a conceptual design usually applied from start to finish. The fact that during IN-SUR-E we conventionally ventilate the baby and during HFOV we do not is inherent to the design of the study. If we would ‘bag’ the baby, recruitment will be lost and we will lose the contrast between the groups (administer surfactant in recruited or non-recruited lung). It is more an “open lung ventilation” that is tested against conventional positive pressure ventilation. Open lung ventilation includes surfactant administration in a recruited lung and avoiding injury after administration. The difference in ventilation during and after surfactant treatment is part of optimal lung volume strategy. This makes our study more of a “comparative effectiveness research” comparing two distinct approaches that consist of several components, rather than a simple randomized controlled trial (RCT) comparing surfactant with and without a recruitment maneuver; (2) failure of CPAP therapy is multifactorial. Local experience with this therapy in the smallest patients and type of CPAP applied seems to play an important role in outcomes. Based on the results of a recent survey on the neonatal respiratory support strategies in the Italian NICUs [33], nCPAP is the most commonly used non-invasive mode of respiratory support, both in the acute and post-extubation phases of RDS. The most commonly used devices in delivering non-invasive respiratory support are the Infant Flow® System (56 %), mechanical ventilators (33 %), and bubble CPAP (16 %). All the 37 NICUs involved in the present study have considerable experience with non-invasive respiratory support. Even though there could be potentially different outcomes according to the different devices used to deliver non-invasive respiratory support pre and post extubation, this should not affect the differences between the two interventions in our study, because of the randomization; (3) some studies do show a reduction in intubation need when N-IMV is used after extubation. Even though there could be potentially different outcomes according to the different non-invasive respiratory strategies used after extubation, it is conceivable that clinicians will apply a specific non-invasive ventilatory support (CPAP or BiPAP or N-IMV) similarly in both groups. Although there might be differences between centers, it will be similar within centers and because we randomize on center, this will not affect the differences between the two groups.

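### Discretionary BiPAP or N-IMV in an open trial can keep an infant out of the oxygen component of the primary outcome, and stratifying by centre does not protect the comparison from unequal use

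*Protocol article*

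**What the plan says.** All references are to the protocol article.

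- **Blinding:** "The study will not be blinded, and the staff performing the study also will take subsequent care of the infants".
- **Surfactant treatment:** BiPAP or N-IMV may be started "to prevent the need for re-intubation in infants of both groups". The decision "will be up to the neonatologist on duty, and will be considered in the final analysis". No start criterion is given.
- **Primary outcome measure:** the result is "a failure if the infant needs mechanical ventilation in the first 72 h". Infants also count as failures "when they are not extubated within 30 min after surfactant administration or when they meet the nCPAP failure criteria after extubation".
- **CPAP failure criteria:** "CPAP failure is defined if they met any of the following criteria". The three criteria are oxygen need, respiratory acidosis and apnea. The oxygen criterion (FiO2 of 0.30 or more for at least 30 min, unless there is rapid deterioration) is expressed for an infant receiving nCPAP. The other two name no interface.
- **Secondary outcome measures:** need for and duration of BiPAP and N-IMV are listed, with no 72 h window.
- **Statistical analysis:** the logistic model contains treatment arm, gestational age, birth weight, antenatal steroids and CRIB score. It has no BiPAP/N-IMV term.
- **Discussion, third limitation:** "some studies do show a reduction in intubation need when N-IMV is used after extubation". Similar use in the two groups is called conceivable. Practice is said to be alike within a centre, and "because we randomize on center, this will not affect the differences between the two groups".

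**The concern.** Non-invasive escalation is chosen after randomisation by clinicians who know the arm. Its declared purpose is to avoid an event that counts in the primary outcome, and the protocol itself says that one form of it may do so. If the arms are escalated differently, the difference passes into the primary result.

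The wording of the oxygen criterion opens a second route. The protocol does not say how an infant on N-IMV who needs an FiO2 of 0.30 or more is to be classified. On a literal reading that infant has not met the oxygen criterion and, if not intubated and free of the other criteria, counts as a success.

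The protocol answers with centre stratification. That controls differences between centres, which is a different problem. At stake is either a false benefit or a masked one, depending on which arm receives more support.

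**Working it through.** **1. The plan's own figure.** Inputs from Sample size: 50% v 30%, two-sided alpha 0.05, power 80%.

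n′ = [1.960·√(2·0.40·0.60) + 0.8416·√(0.50·0.50 + 0.30·0.70)]² / 0.20² = 93.0.

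With the continuity correction, n = (n′/4)·[1 + √(1 + 4/(n′·0.20))]² = 102.8, so 103 per arm. The plan's figure is reproduced and is used below.

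**2. Which infants can leave the outcome.** Combining Primary outcome measure with CPAP failure criteria, for an infant extubated within 30 min and not re-intubated by 72 h:

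| Situation after extubation | Classification on the text |
|---|---|
| Meets any criterion on nCPAP, then moved to BiPAP or N-IMV | Failure already |
| Moved first, then meets acidosis or apnea criterion | Failure; no interface is named |
| Moved to N-IMV first, then FiO2 ≥ 0.30 | Not a failure if read literally |
| Moved to BiPAP first, then FiO2 ≥ 0.30 | Unclear; the protocol calls BiPAP a bi-level form of nCPAP |
| Moved first, and the support itself prevents any criterion | Not a failure |

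The routes out are therefore the last three rows.

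**3. Does centre stratification remove unequal use?** Suppose there is no true effect. In centre c let b be the failure rate without such support, u₀ and u₁ the shares of would-be failures given it in the control and intervention arms, and r the share of those kept out of the outcome.

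Arm rates: b(1 − r·u₀) and b(1 − r·u₁). Difference within the centre: b·r·(u₁ − u₀).

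This difference lies inside each centre, so balancing or stratifying on centre leaves it untouched. It is zero only if u₁ = u₀, and that is the premise the protocol assumes.

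A simulation checked this: 4,000 runs, 37 centres (the number in the Discussion), arms balanced within centre, mean b = 0.50, r = 0.5.

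| Use, control v intervention | Mean false difference | Rejection, unstratified | Rejection, centre-stratified (Mantel-Haenszel) |
|---|---|---|---|
| 30% v 30% | about 0 | 5.3% | 5.3% |
| 30% v 50% | 5.1 points | 11.7% | 11.8% |
| 30% v 60% | 7.4 points | 20.1% | 20.3% |

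**4. Illustrative size.** The documents give neither use by arm nor r, so every shift here is an assumption. The rejection rate is the sum, over all pairs of event counts (x, y), of Bin(x; 103, p₁)·Bin(y; 103, p₂) where the two-sided p-value is below 0.05. Pearson's test is named under Sample size, and Fisher's exact test under Statistical analysis.

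| Rates, no true effect | Pearson | Fisher's exact |
|---|---|---|
| 50% v 50% | 4.6% | 3.3% |
| 50% v 45% | 10.6% | 8.3% |
| 50% v 40% | 30.4% | 25.9% |

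What the shifts require, from b·r·(u₁ − u₀) with b = 0.50:
- r = 0.5, use 30% v 50%: 0.50·0.5·0.20 = 5.0 points.
- r = 0.25, use 30% v 50%: 0.50·0.25·0.20 = 2.5 points (rejection 6.5%, normal approximation).
- r = 0.25, use 30% v 60%: 0.50·0.25·0.30 = 3.8 points (rejection about 8%).
- A 10-point shift needs, for example, r = 0.5 with use of 20% v 60%: 0.50·0.5·0.40. That is an extreme case.

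In the other direction, if extra support in the control arm lowers its 50% to 45% against a true 30%, exact Pearson power falls from 84.7% to 61.4%.

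**The case against.** The best defence is that the protocol sees the issue and partly covers it.

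- It lists differing non-invasive support as a limitation, and its argument rests on similar use within centres as well as on stratification. This is correct, but the premise is assumed, and in an open trial nothing enforces it.
- BiPAP/N-IMV need and duration are already secondary outcomes, so use will be compared by arm. A reader might infer that the plan contains no check at all; the documents do not support that. What is missing is the window that matches the primary outcome.
- A reader might also infer that any infant moved to BiPAP or N-IMV can be turned into a success. The text does not support this either. Infants who have already met a criterion after extubation remain failures, the acidosis and apnea criteria are not tied to nCPAP, and BiPAP is arguably still nCPAP in the protocol's own terms.
- The undertaking to consider this support in the final analysis might be read as a plan to adjust for it. The listed covariates contain no such term, and the details may be in an analysis plan that is not shown. The phrase is only ambiguous.
- The shifts are assumed. This stands: the tables show sensitivity and do not estimate the bias.
- Counting a BiPAP/N-IMV start as failure makes the same unblinded choice an endpoint event. This also stands, so that analysis is a check and not a cure.

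None of this closes the gap for N-IMV with the oxygen criterion, or rescues the inference from centre stratification.

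**Conclusion.** The point holds in limited form. First, the outcome rule as written can class an infant on N-IMV with FiO2 at or above 0.30 as a success when no criterion was met beforehand; for BiPAP the text is unclear. Second, the Discussion's conclusion from randomising on centre is invalid for a within-centre choice made with the arm known. Equal use is an assumption.

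The documents do not show that use will differ, by how much, or in whose favour. If a difference shifted the observed rates by 5 points with no true effect, the false-positive rate would roughly double (4.6% to 10.6% Pearson; 3.3% to 8.3% Fisher's exact). A shift against the intervention would cost power instead. The correction should be made: it is cheap and bears on the primary outcome.

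**What to change.** 1. For outcome classification only, apply the stated oxygen, acidosis and apnea criteria after extubation whatever the non-invasive interface.
2. Report BiPAP/N-IMV use by arm for the first 72 h of life, in addition to the planned overall comparison.
3. Add a sensitivity analysis of the primary outcome in which a BiPAP or N-IMV start within 72 h counts as failure. Label it as a check, since the start is itself an unblinded decision.
4. State that considering this support in the final analysis does not mean adjusting the primary comparison for it. Its use follows randomisation and may depend on the arm, so adjustment could itself bias the effect.
5. Replace the Discussion sentence on randomising by centre with a statement that unequal use between arms remains a possible source of bias.

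No change to clinical management is proposed. The cost is wording and one extra analysis. Need for and duration of this support are already collected, but start times must be recorded well enough for the 72 h cut, and oxygen need must be available for infants on BiPAP or N-IMV. The result will be less simple to present if the two analyses differ.

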#### Caffeine

A loading dose of caffeine citrate (20 mg/kg) will be given immediately after admission to the NICU, followed by a daily maintenance dose of 5–10 mg/kg.

#### Analgesia-sedation

All neonates will receive pre-intubation medications to provide adequate analgesia and sedation while preserving spontaneous respiratory activity during the procedure of surfactant administration, according to the local protocols involving the use of opioids (fentanyl or remifentanil).

### Primary outcome measure

The primary outcome is the need for mechanical ventilation within the first 3 days of life and, therefore, we consider IN-REC-SUR-E or IN-SUR-E a success if mechanical ventilation is not required and a failure if the infant needs mechanical ventilation in the first 72 h. Infants in both groups will be considered to have reached the primary outcome also when they are not extubated within 30 min after surfactant administration or when they meet the nCPAP failure criteria after extubation.

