
### Trial hypothesis

The primary hypothesis of this study is that there will be a reduction in the need of mechanical ventilation in the first 72 h of life (excluding the transient tracheal intubation performed for surfactant administration and the mechanical ventilation administered for lung recruitment) in spontaneously breathing infants born at 24^+0^–27^+6^ weeks’ gestation and failing nCPAP during the first 24 h of life who received an HFOV recruitment maneuver (IN-REC-SUR-E) compared to those receiving no recruitment maneuver (IN-SUR-E) just prior to surfactant administration followed by prompt extubation.

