### Sample size

We hypothesized that a recruitment maneuver (in HFOV modality) before surfactant administration might decrease of the need of subsequent mechanical ventilation during the first 72 h of life from 50 % [2, 5, 7] to 30 %. We calculated that 103 newborns must be enrolled in each group to detect this difference as statistically significant with 80 % power at the 0.05 alpha level using the two-sided Pearson’s chi-square test.

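### The primary outcome is defined two ways: an infant never ventilated beyond the surfactant procedure can be both a success and a failure

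*Protocol article*

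**What the plan says.** All places are in the protocol article.

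- **Primary outcome measure, first sentence.** The outcome is mechanical ventilation in the first 72 h, and either procedure is "a success if mechanical ventilation is not required".
- **Primary outcome measure, second sentence.** Infants in both groups also reach the outcome if still intubated 30 min after surfactant, "or when they meet the nCPAP failure criteria after extubation". The Methods/design part of the Abstract repeats this.
- **Trial hypothesis.** The outcome is ventilation in the first 72 h, "excluding the transient tracheal intubation performed for surfactant administration and the mechanical ventilation administered for lung recruitment". CPAP failure after extubation is not mentioned.
- **Data collection (PICOT summary).** The outcome is need for mechanical ventilation, to 72 h of life.
- **CPAP failure criteria.** Any one of an oxygen, an acidosis or an apnea criterion is enough. None requires that the infant be ventilated.
- **Surfactant treatment.** Infants in both groups may have a second dose by the same method "if they meet the CPAP failure criteria again during the following 12 to 24" hours. Bi-level nCPAP or nasal intermittent ventilation may be used to avoid re-intubation.
- **Sample size.** Subsequent mechanical ventilation is assumed to fall "during the first 72 h of life from 50 % [2, 5, 7] to 30" per cent, "with 80 % power at the 0.05 alpha level using the two-sided" Pearson test, so that "103 newborns must be enrolled in each group".

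**The concern.** A binary primary outcome must put each infant in exactly one class. Here the success sentence and the added component disagree about infants who meet the CPAP failure criteria after extubation but are never ventilated beyond the surfactant procedure. The protocol provides for this course, so it is not a remote case.

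Two things are at stake. First, the trial could report on a different outcome from the one in its hypothesis: avoiding ventilation and avoiding renewed CPAP failure are different claims. Second, the planning rates are tied to ventilation by their wording, so it is unclear whether 103 per arm suits the outcome that will be counted. The missing time limit adds to this. Read literally, criteria met after 72 h would count, whereas ventilation started after 72 h would not.

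**Working it through.** **1. The conflicting case.** Take an infant who is extubated within 30 min of surfactant, meets the CPAP failure criteria again, has a repeat procedure or non-invasive support, and is not otherwise ventilated by 72 h.

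| Place | Class |
|---|---|
| Primary outcome measure, first sentence | success |
| Trial hypothesis (intubation for surfactant and recruitment ventilation excluded) | no event |
| PICOT summary (ventilation only) | no event |
| Primary outcome measure, second sentence | failure |
| Abstract, Methods/design | failure |

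The repeat procedure falls inside the outcome window. Entry requires CPAP failure in the first 24 h of life. If the repeat interval is read as running from the first dose, it ends by roughly 24 + 24 = 48 h of life, before 72 h.

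**2. The plan's sample size.** Inputs from Sample size: 50% v 30%, two-sided 0.05, 80% power. The mean rate is 0.40.

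- Uncorrected: n = [1.96·√(2·0.40·0.60) + 0.8416·√(0.50·0.50 + 0.30·0.70)]² / 0.20² = (1.358 + 0.571)² / 0.04, which rounds up to 93.
- Continuity-corrected: (93/4)·[1 + √(1 + 4/(93·0.20))]² = 102.8, which gives 103.

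The stated 103 is reproduced with the continuity correction. It is not in error for the rates given. With the uncorrected test, power at 103 is Φ[(0.20·√103 − 1.358)/0.678] = Φ(0.99), about 84%.

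**3. What the added component could do.** The documents do not give the share q of never-ventilated infants who meet the criteria again, so q is an assumption, taken as equal in both arms. If the 50% and 30% are pure ventilation rates, each counted rate becomes p + q(1 − p), and the difference shrinks to 0.20·(1 − q). Never-ventilated infants number 103·0.50 + 103·0.70 = 123.6 of 206, and the share q of them changes class.

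| q (assumed) | Counted rates | Infants reclassified | Power at 103 per arm, uncorrected | n per arm for 80%, continuity-corrected |
|---|---|---|---|---|
| 0 | 50 v 30% | 0 | 84% | 103 |
| 5% | 52.5 v 33.5% | 6 | 79% | 116 |
| 10% | 55 v 37% | 12 | 74% | 131 |
| 20% | 60 v 44% | 25 | 63% | 165 |
| 30% | 65 v 51% | 37 | 53% | 208 |

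**4. What the 50% measures.** Sample size labels it a ventilation rate and cites references 2, 5 and 7. The Background gives figures from those same references as CPAP failure rates: 46%, 45% and 50%. The planning rate may therefore already contain some of the added component, and step 3 would then count it twice.

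**The case against.** The strongest reply is that *also* in the second sentence makes the outcome a composite, in which any component is a failure. The Abstract repeats the same components, so the operative rule is stated twice and before results. This is a fair reading, and it weakens any suggestion that the choice is simply left open. It does not repair the text. Under a composite, avoiding ventilation is not sufficient for success, so the success sentence is wrong as written; the hypothesis and the PICOT summary still describe another outcome; and the added component still has no explicit time limit.

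The second reply is that the power figures rest on invented shares and that the 50% may already be a CPAP failure rate. That stands. The table shows sensitivity and does not estimate a loss.

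Third, the criteria-based component has merit in an unblinded trial whose staff also give the later care, because it depends less on the decision to intubate. That also stands, and it is why the choice of definition should remain with the sponsor.

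Two stronger readings are tempting but not supported:

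- A reader might infer from the Trial hypothesis that procedural ventilation is excused only in the IN-REC-SUR-E arm, which would bias the comparison in its favour. But intubation for surfactant is excused in both arms, and both groups have the same 30 min window, which would serve no purpose for controls if ventilation inside it already counted. A strict reading would also catch the oscillation that continues after recruitment in the IN-REC-SUR-E arm. What remains is incomplete wording.
- A reader might infer that an infant moved to bi-level support or nasal intermittent ventilation cannot meet the failure criteria, because the oxygen criterion refers to nCPAP. But the protocol itself calls BiPAP bi-level nCPAP, and the acidosis and apnea criteria carry no such restriction.

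**Conclusion.** The concern holds as an inconsistency in the primary outcome. The same never-ventilated infant is classed both ways, by a course the protocol provides for, and the hypothesis and the PICOT summary do not match the fuller definition. This rests on the text alone and needs no assumption.

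Its numerical size is unknown. If the planning rates are pure ventilation rates, reclassifying even 5% of never-ventilated infants in each arm takes power from about 84% to 79%, and 30% takes it to 53%. If those rates already include CPAP failure, the loss is smaller or absent, but the Sample size section then mislabels them. The documents do not settle which applies. They do not show that the trial is underpowered, that 103 is miscalculated, or that the definition favours either arm.

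**What to change.** 1. State one primary definition, with an explicit 72 h limit on every component, and reconcile the Abstract, Trial hypothesis, Sample size, Primary outcome measure and PICOT summary to it.
2. If the composite is kept, correct the success sentence, restate the hypothesis and the planning rates for the composite, and report ventilation alone as a pre-specified sensitivity analysis. If ventilation alone is chosen, report the composite as that sensitivity analysis.
3. State whether a repeat procedure followed by extubation within 30 min counts as an event.
4. Say in Sample size whether the 50% is a ventilation rate or a CPAP failure rate, and check 103 per arm against the outcome chosen.
5. As a clarification only, word the exclusion in the Trial hypothesis to cover ventilation around surfactant within the 30 min window in both arms.

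The cost is wording, a check of the planning rates and one additional analysis; care does not change. The real trade-off is in step 2. Ventilation alone matches the hypothesis but moves the component less open to unblinded intubation decisions into a sensitivity analysis. The composite keeps that component in the primary analysis but requires the hypothesis and planning rates to be restated, and possibly a larger sample.
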